### 2.24. Lost to Follow Up

A participant was considered lost to follow-up if they were repeatedly unable to be contacted by the study site.

### 2.25. Ethical Considerations

This study was conducted in accordance with consensus ethical principles derived from international guidelines including the Declaration of Helsinki and the Council for International Organizations of Medical Sciences’ International Ethical Guidelines, applicable ICH Good Clinical Practice Guidelines, and applicable laws and regulations.

The informed consent procedure included the use of simplified explanations of the digital tools involved, supported by visual aids and step-by-step demonstrations when necessary. Participants were encouraged to ask questions, and family caregivers could be involved in the discussion to facilitate comprehension and support decision-making. To verify participant understanding prior to obtaining consent, study staff provided additional explanations when needed and confirmed that participants clearly understood the study procedures, including the digital aspects, before consent was finalized. In addition, throughout the trial, participants had access to ongoing support from the research team to address potential difficulties with the digital components of the intervention. This support aimed to minimize barriers to participation and reduce the risk of digital exclusion.

The study and its amendments were approved by the Ethics Committee of IRCCS MultiMedica and CET Lombardia 5, Prot.nr.509/24 and Prot.nr.353/25. This protocol was deposited in Zenodo and is accessible at https://zenodo.org/records/18632447 (accessed on 13 February 2026).

## 3. Results

From May 2024 to December 2025, 589 individuals were assessed for eligibility at the two centers. Among them, 147 patients were excluded because they met the exclusion criteria: more than one third (39%) were unable to use electronic devices and 21% were clinically unstable. Among the minor reasons for exclusion were MMSE < 15 (6%) and age < 65 years (4%). Therefore, we screened 442 individuals with recent ACS and AHF who fulfilled the inclusion criteria and were considered eligible for the trial. Among those eligible, 233 declined to participate in the study while two individuals could not be enrolled because they died during hospitalization. The most common reason for declining participation in the trial was the perceived complexity of being compliant with a demanding program, or the willingness to learn how to use the dedicated eHealth platform, a motivation cited by 46% of the eligible individuals approached. Overall, 19% complained about the lack of a caregiver. The remaining 209 people were enrolled in the study and assigned to one of the two groups through randomization. Two patients assigned to the control group dropped out before completing exams or questionnaires and one subject in the intervention group died before discharge (Figure 3). We compared included subjects with the subgroup of subjects who declined to participate with complete data about age, sex and type of cardiac event. The included population was representative of the eligible individuals in terms of age and sex but patients who declined were more likely to have a diagnosis of AHF compared with included individuals (58% vs. 42%, *p* = 0.0078).

Among people undergoing randomization, 103 were assigned to the eHealth intervention group and 103 to the standard-of-care control group. The baseline demographic and clinical characteristics of the two groups are presented in Table 1 while the overall characteristics of the population with the relative number of observations for each variable are shown in Table 2. Clinical characteristics were comparable in the two groups, with the exception of sex and SPPB (Table 1). Overall, the mean (±SD) age of the patients was 77 ± 9 years, and 145 subjects (70.4%) were male. The mean BMI was 25.8. More than half of the patients had ACS (55.3%). As expected, most of the people were receiving lipid-lowering medications (77.5%), antiplatelet drugs (56.4%), and one or more anti-hypertensive medications.

## 4. Discussion

The efficacy of eHealth-based, home-delivered CR interventions on frailty is debated [7]. To address this gap, we designed a randomized trial evaluating whether an eHealth CR program, compared with standard care, can reduce the prevalence or degree of frailty in patients >65 years hospitalized for AHF or ACS. Here we outline the trial protocol and report the baseline characteristics of the enrolled participants.

The number of enrolled individuals is lower than the planned sample size for the primary outcome, but sufficient for the co-primary outcomes. Thus, the study will be powered to detect a difference in the mean level of frailty but not to observe a difference in the prevalence of frailty considered as a binary variable, unless a higher-than-expected efficacy of the intervention emerges. Indeed, the study now reaches a power of 55% for the primary outcome when considering an expected difference of 13% in the final prevalence of frailty, while a difference of 17% in the prevalence of frailty would be needed to obtain a significant result. This aspect is of relevance, especially in case of non-significant findings.

The lower-than-expected enrollment capacity is attributable to the high rate of refusal to participate due to the reported inability or fear of using technological devices such as a tablet. These phenomena commonly, referred to as “digital illiteracy” and “technophobia”, are common in the oldest old and particularly pervasive in Italy [24]. As a result, we had to amend the protocol after the start of the study to lower the cutoff for age of inclusion in the study. We believe that this does not represent an issue since, as discussed, frailty represents a continuum with a broad spectrum of conditions that should be addressed as early as possible and not only when severe comorbidities are present [9,10]. In this respect, this consideration also emphasizes the relevance of the results, which will demonstrate whether an eHealth-based, multidomain intervention is able to affect the degree of frailty when considered as a continuous, and not binary, variable.

Independently of the results that we will observe, it is important to note that digital illiteracy represents a key limit for the wide diffusion and implementation of such programs in real-life scenarios. We observed that roughly 20% of the screened individuals could not be enrolled due to the observed inability to use simple technological devices, while almost half of those screened refused to participate due to a lack of willingness to engage in a home-based program or for a refusal to learn how to use the telemedicine software. Notably, the idea of using remote intervention based on telemedicine and telemonitoring was conceived to provide an alternative for older people with a high degree of disability and thus those who were struggling to participate in in-person programs and visits. Thus, even if the eHealth approach is effective, it will remain of limited usefulness if it cannot be implemented in a wide range of individuals. Even though common sense suggests that future generations of old populations, who grew up in the technological era, will not face such issues, older subjects living with these limitations at present should be helped to learn basic technological skills to have access to such programs.

Another aspect to be considered is that we opted to enroll people with either acute HF or ACS since they are both post-acute cardiac events. However, individuals with these conditions may differ in terms of baseline functional trajectory, symptom limitations (e.g., dyspnea/fatigue burden), medication profiles, contraindications, and expected recovery patterns. This aspect might generate heterogeneity in the response to the intervention.

Relative to the composition of the groups, these are well balanced, as expected by the randomization process. The only variables not balanced are sex and the SPPB. Thus, the analyses will be adjusted for such covariates, given their known relationship with the primary outcomes [25]. Cox models and ANCOVA, both adjusted for these unbalanced variables, were used to compare the prevalence and the degree of frailty, respectively. A sensitivity analysis using propensity score matching was also performed. In the active arm of the trial, 45 people performed low-level-intensity exercises and the others underwent a high-level program. Given this limited sample, subgroup analyses are not adequately powered and cannot explore whether the intervention is more effective in people with a low SPPB score, despite the prior literature suggesting that the frailest individuals (i.e., SPPB < 10) would show greater improvement [26].

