### 2.20. Sample Size Estimation

From the literature, frailty at discharge is expected to be about 40% in the overall study population [17,18]. We expect frailty reversal in Groups A and B of 48% and 15%, respectively [8], so frailty at the end of follow-up is hypothesized to be 21% in Group A and 34% in Group B. To achieve 80% power in detecting a 13% difference in frailty prevalence between Groups A and B after the intervention, with an alpha error of 5%, a sample size of 370 subjects is needed. Considering about a 22% dropout rate, a total of 450 patients are required.

Considering that recent trials do not consider frailty as a binary outcome, but as a continuous variable [23], and that an improvement of 1 unit in the EFT scale is associated with a 28% lower mortality incidence and thus represents a clinically meaningful phenomenon [11], we also calculated the sample size needed to observe a difference in the mean level of EFT between the two groups. Considering that: 1—using real data collected in our units in other similar studies, the mean EFT at baseline is 2.25 ± 1.25; 2—assuming an improvement of 1 unit (minimal clinically important difference, i.e., the smallest difference in score that benefits the patient) and therefore a mean score at the end of the study of 1.25 ± 1.25 [11]; 3—assuming a power of 90% and alpha of 5%; and 4—assuming a 30% improvement in the control group treated with the standard of care (and thus expecting a mean EFT of 1.95 in this group) and maintaining the same SD for all, it follows that 136 individuals are needed to observe a difference in the mean level of EFT score at the end of the trial. Considering also a 22% possible dropout rate, a sample size of 166 people is needed for this analysis. The same calculation using the SPPB as the metric of interest provided similar results.

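### The Discussion labels 17 points as the difference needed for significance when it is the 80%-power detectable difference, and its 55% power assumes that no patient drops out

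*Protocol article*

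**What the plan says.** Section 2.20 builds the binary endpoint from a baseline rate and two reversal rates. The baseline is stated first: "frailty at discharge is expected to be about 40% in the overall study population". The reversal rates come next: "We expect frailty reversal in Groups A and B of 48% and 15%, respectively". The two together give the planned end-of-study rates: "frailty at the end of follow-up is hypothesized to be 21% in Group A and 34% in Group B". For 80% power to detect those 13 points, the article concludes "with an alpha error of 5%, a sample size of 370 subjects is needed". Dropout is then added: "Considering about a 22% dropout rate, a total of 450 patients are required".

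Section 2.22 limits the frailty-prevalence analysis to patients whose EFT score was measured at both baseline and follow-up.

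Table 1 shows 103 patients per arm. Table 2 gives a baseline frailty prevalence of 63/206 (30.58%).

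The Discussion (section 4) re-evaluates the endpoint at the achieved enrolment: "the study now reaches a power of 55% for the primary outcome when considering an expected difference of 13" percentage points, "while a difference of 17% in the prevalence of frailty would be needed to obtain a significant result". It adds that this matters especially if the findings are not significant. Section 2.2.1 already says that power for prevalence is below plan and treats the endpoint as exploratory.

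**The concern.** The Discussion offers two numbers as the guide for reading a null result, and each can mislead.

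The 17 points are described as a significance threshold. The difference that an observed result must exceed to give p<0.05 is always smaller than the true difference that yields 80% power. Confusing them tells the reader that, for example, an observed 15-point difference could not be significant.

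The 55% is presented as the power the study now has. Section 2.20 added patients to cover dropout, and section 2.22 removes patients without follow-up EFT. A power figure at the achieved size should carry the same allowance, or say that it does not.

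The 13 points are still called expected, although the 40% prevalence from which they were derived was not observed.

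**Working it through.** **Method.** Unadjusted two-proportion test, two-sided alpha 5%, pooled variance under the null, n per arm:

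power = Φ{[d − 1.96·√(2·m(1−m)/n)] / √([pA(1−pA) + pB(1−pB)]/n)}, where d = pB − pA and m is the mean of pA and pB.

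**Step 1: reproduce the planned size.** With 21% v 34%, n = [1.96·√(2×0.275×0.725) + 0.8416·√(0.1659 + 0.2244)]² / 0.13² = (1.2377 + 0.5258)² / 0.0169 = 184.01. This rounds up to 185 per arm, or 370 in total, so the method matches the plan's.

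**Step 2: reproduce the 55%.** At n = 103 the null term is 1.96 × 0.06222 = 0.1220 and the denominator is √(0.3903/103) = 0.0616. Power = Φ[(0.13 − 0.1220)/0.0616] = Φ(0.131) = 55.2%. The stated figure is reproduced with all 206 patients evaluable.

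**Step 3: apply the plan's dropout.** 206 × 0.78 = 160.7, about 161 evaluable or 80 per arm. The null term is 1.96 × 0.0706 = 0.1384 and the denominator 0.0698. Power = Φ[(0.13 − 0.1384)/0.0698] = Φ(−0.120) = 45.2%. The 450 in section 2.20 in fact allows for 1 − 370/450 = 17.8% loss; at that rate (about 85 per arm) power is about 47%.

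**Step 4: identify the 17 points.** For 17% v 34% at n = 103, the null term is 1.96 × 0.06074 = 0.1190 and the denominator 0.0596. Power = Φ[(0.17 − 0.1190)/0.0596] = Φ(0.855) = 80.4%. Solving for exactly 80% power gives:

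| Per arm | Control fixed at 34% | Intervention fixed at 21% |
|---|---|---|
| 103 | 16.9 points | 17.8 points |
| 80 | 18.9 points | 20.4 points |

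**Step 5: find the significance threshold.** The smallest observed difference with p<0.05 solves d = 1.96·√(2·m(1−m)/n), with m = 0.34 − d/2 when the control rate is 34%.

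- n = 103: d = 12.2 points.
- n = 80: d = 13.8 points.
- Check with counts: 21/103 v 35/103 (13.6 points) gives p = 0.028 by chi-square and 0.041 by Fisher's exact test.
- For 17 points to be the threshold, n would have to be 1.96² × 2 × 0.255 × 0.745 / 0.17² = 50.5, about 51 per arm. That means losing about half of the 103.

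**Step 6: use the observed baseline with the planned reversal rates.** Group A: 0.3058 × (1 − 0.48) = 15.9%. Group B: 0.3058 × (1 − 0.15) = 26.0%. The difference is 10.1 points. Power is Φ(−0.182) = 42.8% at 103 per arm and Φ(−0.395) = 34.7% at 80 per arm.

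**The case against.** A reader might infer that both Discussion figures are miscalculated. They are not. The 55% is right for 21% v 34% with 206 evaluable patients, and 17 is a correct number with the wrong description.

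A reader might also infer that the lower baseline necessarily lowers power. The documents do not support that. The 55% is stated as conditional on a 13-point difference. If 13 points are kept and the control rate is 26.0%, power rises to 65.6% at 103 per arm and is 54.7% at 80 per arm. The lower figures follow only if the reversal rates are held fixed. That is how section 2.20 builds its difference, and 13 points from a 30.6% baseline would need more efficacy than planned, but it remains a choice. Applying the reversal rates to each arm's own baseline (29.13% and 32.04% in Table 1) gives 15.1% v 27.2%, a 12.1-point difference, and power of 57% or 46%; part of that difference is the baseline gap between arms.

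Nor may 22% be read as observed attrition. The article does not report follow-up losses, so 45% is power under the plan's assumption.

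The thresholds in step 5 are not universal either. They depend on the control rate and the test: at 103 per arm with 35 control events, Fisher's exact test needs 13.6 points. The planned analyses are adjusted models, so an unadjusted threshold is only a guide.

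Finally, the article already concedes low power and calls the endpoint exploratory. That stands, and it limits the consequence: the correction sharpens the message without reversing it.

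**Conclusion.** The point holds in limited form and should be corrected.

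- **The 17 points.** The description is wrong as written. It is the 80%-power difference at 103 per arm with a 34% control rate. The observed difference that reaches p<0.05 is about 12 points at 103 per arm and about 14 at 80 per arm, with control at 34% and an unadjusted two-sided test.
- **The 55%.** The arithmetic is right, but the figure depends on an unstated assumption of no dropout, which conflicts with sections 2.20 and 2.22. Under the planned 22% dropout it is about 45%, 10 points lower.
- **The 13 points.** They depend on a 40% baseline. The value of about 10 points, with 43% or 35% power, is a scenario conditional on the planned reversal rates.

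The conclusion that the study is underpowered for prevalence is unchanged. What changes is how a non-significant result, or an observed difference between about 12 and 17 points, would be read.

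**What to change.** In the Discussion:

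1. Remove the clause that makes 17 points a condition for significance. Describe it as the true difference detectable with 80% power if all 206 patients are evaluable and the control rate is 34%. Add that the corresponding difference is about 19 points with about 161 evaluable.
2. Restate power for 21% v 34% as about 45% under the planned 22% dropout, and 55% only with no dropout. Once follow-up is complete, replace the assumed evaluable number with the actual one.
3. State that the 13 points come from a 40% baseline prevalence. Add that the planned reversal rates applied to the observed 30.6% give 15.9% v 26.0%, about 10 points, with power of about 43% (206 evaluable) or 35% (161 evaluable). Present this as conditional on those reversal rates.
4. If a significance threshold is quoted at all, give the control rate, the number per arm and the test with it.

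The cost is a few sentences. Design, enrolment and analysis are unaffected; the stated power becomes less favourable.

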### 2.21. Randomization

Patients were randomly assigned in a 1:1 ratio to the intervention or control group through permuted-block randomization with varying block sizes. Randomization lists were center-specific and they were created using SAS^®^ Proc Plan permuted-block randomization. A list was created for each center. The lists were created with block sizes of 2, 4, and 6. The order of block permutations was then randomized within each list to avoid predictability. A seed was set for generating the list so that it could be reproduced if necessary. Patient allocation was performed via a centralized email system.

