### 2.22. Data Collection and Statistical Analysis

Study data were collected in the eCRF of an electronic web-based database, where each patient is identified by a randomly assigned alphanumeric code that is center-specific.

Baseline data were analyzed through descriptive analyses. Results for the overall population and for both Groups A and B are presented. Categorical variables were presented as frequencies and percentages and compared between the two groups by Chi-square test of Fisher’s exact test. Continuous variables were summarized by mean ± standard deviation and tested for normality distribution by Kolmogorov–Smirnov test. Since all variables were not normally distributed, the non-parametric Wilcoxon–Mann–Whitney U test will be used to compare baseline variables between groups. The prevalence of frail patients in the two groups is indicated as an EFT score ≥ 3. For the planned analyses, mixed models, adjusted for unbalanced variables, will be used to account for different times to follow-up. Only people with available measures of EFT at both baseline and follow-up will be included in the analyses relative to the prevalence of frailty and EFT as a continuous variable, while only individuals with available measures of SPPB at both baseline and follow-up will be included in the analyses for this endpoint. For the other covariates, missing data will be imputed through regression models. Given the limited sample size, subgroup analyses are not planned.

All analyses were performed by using SAS Software version 9.4. Tests will be considered significant for a *p* value < 0.05.

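### Index diagnosis (AHF or ACS) is left out of the outcome models because covariates are chosen by baseline imbalance, although the article itself links diagnosis to recovery

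*Protocol article*

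**What the plan says.** On the patients, the Discussion (section 4) says that "individuals with these conditions may differ in terms of baseline functional trajectory, symptom limitations", goes on to medication, contraindications and expected recovery, and concludes: "This aspect might generate heterogeneity in the response to the intervention".

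On covariates, section 2.22 states that "mixed models, adjusted for unbalanced variables, will be used to account for different times to follow-up". The Discussion applies the rule: "The only variables not balanced are sex and the SPPB. Thus, the analyses will be adjusted for such covariates". It adds that these two variables are known to relate to the outcomes, but what selected them was the baseline comparison. The Discussion also names Cox models and ANCOVA instead of mixed models, with the same two covariates.

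On design, section 2.21 says "Randomization lists were center-specific"; diagnosis is not a stratum. On subgroups, section 2.22 says: "Given the limited sample size, subgroup analyses are not planned".

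Table 1 gives 60 ACS and 43 AHF patients in the intervention arm, and 54 and 49 in the control arm (p = 0.400). Table 2 shows diagnosis recorded for all 206.

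**The concern.** A covariate earns its place in a randomized comparison by predicting the outcome. Whether it happens to differ between arms at p < 0.05 is a poor guide: a strong predictor can pass that test and still be worth adjusting for, while a weak one can fail it. Under the stated rule diagnosis drops out because its p-value is 0.400, although the article's own account of recovery makes it a likely predictor of follow-up EFT and SPPB.

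Three things are at stake: precision of the pooled estimate, a small chance imbalance left uncorrected, and the absence of any figure showing whether the average effect holds in AHF and in ACS. The last bears on who the result describes, since the Results report that "patients who declined were more likely to have a diagnosis of AHF compared with included individuals".

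These are separate matters. A main-effect covariate serves the first two. It says nothing about differing response.

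**Working it through.** **The plan's own figures.** Section 2.20 assumes an EFT SD of 1.25 ("the mean EFT at baseline is 2.25 ± 1.25") and end-of-study means of 1.25 and 1.95, a difference of 0.70, with 90% power and 5% alpha (two-sided assumed).
- n per arm = 2 × (1.960 + 1.282)² × 1.25² / 0.70² = 67.01, rounded up to 68. The total is 136, as stated.
- The uncorrected chi-square for diagnosis by arm is 0.707, p = 0.400, as in Table 1.

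**Effect of leaving diagnosis out.** The ACS share differs by 60/103 − 54/103 = 0.058. If follow-up EFT differs by D points between AHF and ACS patients, the unadjusted contrast shifts by 0.058 × D. The share of outcome variance explained by diagnosis is D² × 0.5534 × 0.4466 / 1.25². The documents give no D, so a range is assumed.

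| Assumed D | Shift in EFT contrast | Variance explained | Narrowing of CI |
|---|---|---|---|
| 0.25 | 0.015 | 1.0% | 0.5% |
| 0.50 | 0.029 | 4.0% | 2.0% |
| 1.00 | 0.058 | 15.8% | 8.2% |

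The last column is 1 − √(1 − variance explained). It is an upper guide, because sex and SPPB may already take up part of the same variation. With 22% dropout the pooled SE is 1.25 × √(2/80.3) = 0.197, so even the largest shift is about 0.3 SE.

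**What estimates by diagnosis could show.** SE = 1.25 × √(1/n₁ + 1/n₂), half-width = 1.96 × SE, and power = Φ(0.70/SE − 1.96), first with full retention and then with 78%.

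| Group (arms) | SE | Half-width | Power for 0.70 |
|---|---|---|---|
| ACS (60 v 54) | 0.234 to 0.265 | 0.46 to 0.52 | 85% to 75% |
| AHF (43 v 49) | 0.261 to 0.296 | 0.51 to 0.58 | 76% to 66% |
| Interaction | 0.351 to 0.397 | 0.69 to 0.78 | 51% to 42% |

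The interaction SE is the root of the summed squares, for example √(0.265² + 0.296²) = 0.397. Its power is for the extreme case in which the whole 0.70 effect falls in one diagnosis and none in the other. The interaction detectable with 80% power is 2.80 × SE, that is 0.98 to 1.11 points.

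**SPPB.** Baseline SPPB exists for 171 of 206, and section 2.22 requires both baseline and follow-up values. At 78% retention, 171 × 0.78 ≈ 133 patients remain, against 206 × 0.78 ≈ 161 for EFT. If the missing values are spread evenly over the diagnoses, that leaves about 74 ACS and 60 AHF patients across both arms.

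**Tilt of the enrolled mix.** Assume the decliners with known diagnosis (58% AHF) stand for all 233, and take 45% AHF among the 209 enrolled. The eligible pool is then (0.58 × 233 + 0.45 × 209)/442 ≈ 52% AHF. If the entire 0.70 effect lay in one diagnosis, reweighting by 7 percentage points would move the average by 0.07 × 0.70 ≈ 0.05 EFT points.

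**The case against.** The strongest reply is that the absence of subgroup analyses is a disclosed choice with a sound reason. That stands. The interaction is too imprecise to tell the diagnoses apart, and the within-diagnosis power of 66% to 85% concerns detecting a full 0.70 effect in each group, not a difference between them. Offering descriptive intervals is a preference.

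It is also fair that the imbalance is minor, that the tilt towards ACS is small, and that an unseen analysis plan or the full protocol may say more. The covariates of the propensity-score sensitivity analysis are not listed, so diagnosis may enter there. None of this rescues the covariate rule, which the article states outright and which excludes diagnosis from the main models.

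Two stronger readings are tempting. A reader might infer that the authors predict different responses. They say only that diagnosis might produce heterogeneity, with no direction or size. A reader might also infer that the pooled result can be applied to neither group. That does not follow: the randomized contrast is a valid average for the patients enrolled, and what is missing is evidence on how that average divides.

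**Conclusion.** The point holds as a weakness in how covariates are chosen, not as a flaw that invalidates the comparison. Diagnosis is complete, measured before randomization and, by the article's own reasoning, plausibly prognostic, yet an imbalance test keeps it out.

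The cost to the EFT estimate is small: a shift of 0.015 to 0.058 points and a confidence interval up to about 8% wider than it need be, under assumed AHF–ACS gaps of 0.25 to 1.0. These figures rest on SD 1.25 and the Table 1 counts. The sponsor's reason for not testing subgroups is supported by the numbers.

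**What to change.** In section 2.22, name index diagnosis as a fixed covariate in the EFT, SPPB and prevalence models, on prognostic grounds and regardless of its imbalance p-value. State how patients with both conditions are classed: section 2.1 admits AHF and/or ACS, while Table 1 treats the two as exclusive (114 + 92 = 206).

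Optionally, report the arm effect with a 95% CI in AHF and in ACS, labelled descriptive and exploratory, with no significance claim. State the interaction half-width of about 0.7 to 0.8 EFT points and the lower precision for SPPB. The Discussion describes the adjusted models in the past tense; if outcomes have already been analysed, label the added covariate and these estimates post hoc.

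The covariate costs one parameter and no new data. Under the planned prevalences about 80.3 × (0.21 + 0.34) ≈ 44 patients would be frail at follow-up, so the prevalence model would have about 11 per parameter for arm, sex, SPPB and diagnosis. The optional table costs wide intervals that readers may over-interpret.

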### 2.2. Study Endpoints

#### 2.2.1. Primary Endpoints

The primary endpoint is to assess whether a home-based TR program significantly reduces the prevalence of frailty in comparison to usual care in older individuals hospitalized for ACS and/or AHF. Frailty status is defined as having an Essential Frailty Toolset (EFT) score (ranging from 0 to 5) ≥ 3 [8].

Since the recent literature suggests that frailty is a progressive continuum and not a present/absent condition [9,10] and considering that small improvements in the degree of frailty are associated with tangible benefits [11], the mean degree of frailty was considered as a co-primary endpoint. In particular, mean differences between groups at the end of treatment in the EFT and Short Physical Performance Battery (SPPB) scales were set as co-primary outcomes after the start of the enrollment due to the considerations reported above. After termination of the enrollment, we observed that the study is powered to detect a difference in these co-primary outcomes, while the power for the primary outcome of frailty prevalence is lower than initially planned. Thus, this and the other secondary endpoints will be considered as exploratory.

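### The adjustment set is chosen by baseline p-values (sex and SPPB), so neither baseline EFT nor centre, the randomisation stratum, is in the stated set

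*Protocol article*

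**What the plan says.** Section 2.22 (Data Collection and Statistical Analysis) states that "mixed models, adjusted for unbalanced variables, will be used to account for different times to follow-up". Section 3 (Results) identifies the imbalance: "Clinical characteristics were comparable in the two groups, with the exception of sex and SPPB". Section 4 (Discussion) turns this into the covariate list: "The only variables not balanced are sex and the SPPB. Thus, the analyses will be adjusted for such covariates". It adds that both variables are known to be related to the primary outcomes, and then describes the models differently from section 2.22: "Cox models and ANCOVA, both adjusted for these unbalanced variables, were used to compare the prevalence and the degree of frailty, respectively".

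Three other statements bear on the point:

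- The co-primary comparisons in section 2.2.1 are "mean differences between groups at the end of treatment in the EFT and Short Physical Performance Battery (SPPB) scales", so they compare final scores.
- Section 2.22 defines the EFT analysis set: "Only people with available measures of EFT at both baseline and follow-up will be included in the analyses relative to the prevalence of frailty". The same applies to EFT as a continuous variable.
- Section 2.21 says "Randomization lists were center-specific", with permuted blocks within each list. Centre is not mentioned in any described analysis.

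**The concern.** A baseline significance test asks whether chance could explain a difference that, after proper randomisation, is known to be due to chance. It does not show whether a variable predicts the outcome, and prediction is what makes adjustment useful.

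The rule has three awkward results here.

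- It treats the two co-primary scales unequally by accident. SPPB is adjusted for its own baseline because its p-value was 0.046. EFT is given no such term, because its p-value was 0.298. Yet the article's own supporting reason, a known relationship with the outcome, applies at least as well to the same scale measured earlier.
- It is fragile. Whether SPPB counts as unbalanced depends on the test used (see the check below).
- It passes over centre. The lists were separate for each site, and the sites differ in kind: a cardiovascular department and a cardiac rehabilitation unit.

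If the stated set is taken literally, the EFT analyses lose some precision that costs nothing to recover. Part of a small baseline difference in the intervention's favour also stays in the final comparison. In an unblinded trial, choosing covariates after seeing baseline data is also harder to defend than a list fixed on prognostic grounds.

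**Working it through.** **1. The planned figure.** Section 2.20 gives final means of 1.25 and 1.95 (difference 0.70), SD 1.25, 90% power and alpha 5%. The two-sided two-sample formula gives 68 per arm, or 136, as stated. No covariate is assumed in it.

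**2. The selection rule.** In Table 1 only sex (p = 0.001) and SPPB (p = 0.046) are below 0.05.
- Sex: 83/103 v 62/103 gives chi-square 10.27, p = 0.001, which reproduces.
- SPPB: 9.11 ± 3.46 v 8.27 ± 3.55. Table 2 shows 171 patients with a value. With an assumed 86/85 split, a t-test on these summaries gives p of about 0.12, against 0.046 from the Mann-Whitney test. With the other test, only sex would be selected.

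**3. The baseline EFT gap.** 1.69 - 1.89 = -0.20. Pooled SD = √[(1.19² + 1.23²)/2] = 1.210. SE = 1.210 × √(2/103) = 0.169. The 95% CI is -0.53 to 0.13 and the standardised difference is 0.17. Higher EFT is frailer (section 2.6), so the gap favours the intervention. The SPPB gap (+0.84, pooled SD 3.505, standardised 0.24) also favours it.

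**4. What baseline EFT adds when SPPB is already in the model.** The article gives no correlations, so these are assumed:
- ρ, baseline EFT with final EFT: 0.5 or 0.7
- s, baseline SPPB with final EFT: -0.3 or -0.5
- r, baseline EFT with baseline SPPB: -0.3, -0.5 or -0.7

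Formulas, with equal SDs at both times, SPPB treated as fully observed, and sex ignored:
- R² with SPPB only = s²
- R² with both = (ρ² + s² - 2ρsr)/(1 - r²)
- Variance ratio = (1 - R² both)/(1 - R² SPPB)
- EFT gap left after SPPB = -0.20 - r × (1.210/3.505) × 0.84, which is -0.113, -0.055 and +0.003 for the three values of r
- Carry-over = [(ρ - sr)/(1 - r²)] × gap left

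| r | ρ | s | variance ratio | carry-over |
|---|---|---|---|---|
| -0.3 | 0.5 | -0.3 | 0.797 | -0.051 |
| -0.3 | 0.5 | -0.5 | 0.821 | -0.043 |
| -0.3 | 0.7 | -0.3 | 0.551 | -0.076 |
| -0.3 | 0.7 | -0.5 | 0.557 | -0.068 |
| -0.5 | 0.5 | -0.3 | 0.821 | -0.026 |
| -0.5 | 0.5 | -0.5 | 0.889 | -0.018 |
| -0.5 | 0.7 | -0.3 | 0.557 | -0.040 |
| -0.5 | 0.7 | -0.5 | 0.640 | -0.033 |
| -0.7 | 0.5 | -0.3 | 0.819 | +0.002 |
| -0.7 | 0.5 | -0.5 | 0.941 | +0.001 |
| -0.7 | 0.7 | -0.3 | 0.483 | +0.003 |
| -0.7 | 0.7 | -0.5 | 0.680 | +0.002 |

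Residual variance therefore falls by 6-20% at ρ = 0.5 and by 32-52% at ρ = 0.7. Carry-over runs from about 0 to 0.08 points, at most 0.076/0.70 = 11% of the planned difference.

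**5. Power for mean EFT without any covariate.** 206 less 22% is about 160 evaluable, or 80 per arm. SE = 1.25 × √(2/80) = 0.198, and power at 0.70 is about 94%.

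**6. Centre.** No by-centre data are given, so no figure can be computed.

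**The case against.** The strongest reply is that nothing in the article excludes baseline EFT. For a score measured twice, ANCOVA often means adjustment for the baseline score. A mixed model can carry baseline as a covariate or as a repeated response. Requiring EFT at both visits makes most sense if the baseline value is used. The unbalanced variables could then be additions to a baseline term taken for granted. This stands as a reason not to claim omission. It does not rescue the rule, because both passages define the set by imbalance and the Discussion names its only members.

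A second reply is that a journal article leaves model detail to fuller documents. That would answer a complaint about silence. Here the article states a selection rule and its result, and it gives two different model families.

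A reader might also infer larger consequences, which the documents do not support:

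- *A variance cut of 25-49% (ρ² at 0.5 and 0.7) and a carry-over of 0.10-0.14 points (ρ × 0.20).* These compare with a model that has no useful covariate. SPPB is already declared, and it overlaps with EFT because both include chair-rise performance.
- *A mean-EFT analysis short of patients.* Section 2.20 asks for 166 including dropout, and 206 were included. The shortfall concerns frailty prevalence.
- *Systematic bias.* The 0.20 gap is compatible with chance. It is an imbalance in this sample, not a flaw in the randomised comparison.
- *Invalid standard errors from leaving out centre.* Ignoring a prognostic stratum usually makes them too wide, and the size here is unknown.

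**Conclusion.** The point holds as a criticism of how the covariates are chosen. The stated set consists of the two variables with baseline p below 0.05. It names neither the baseline value of EFT nor the stratification factor. Whether baseline EFT is in the model is unclear. It would be wrong to report it as omitted.

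The consequence is modest to moderate and rests on assumed correlations. If baseline EFT is absent, adding it to a model with SPPB lowers residual variance by about 6-20% (ρ = 0.5) or 32-52% (ρ = 0.7), and prevents a carry-over of about 0-0.08 EFT points. The planned mean-EFT comparison does not depend on this for adequate power. The improvement is still worth making, since the variables are already collected and a fixed list removes doubt about data-driven choice.

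**What to change.** In section 2.22, replace the phrase "mixed models, adjusted for unbalanced variables, will be used" with a fixed covariate list, and make the Discussion agree:

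- mean EFT and EFT ≥ 3: baseline EFT, centre, sex and baseline SPPB;
- mean SPPB: baseline SPPB, centre and sex.

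Sex and SPPB stay because they are already declared. The reason given should be prognosis and the randomisation design. Table 1 p-values should play no part in selection.

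Reconcile section 2.22, which specifies mixed models, with the Discussion, which specifies ANCOVA for degree and Cox models for prevalence, so that each endpoint has one named primary model. If baseline EFT was always intended, the same sentence confirms it.

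The cost is a few sentences and no new data. The Discussion speaks of the models in the past tense, so if any have been run they need refitting, and the date and reason for the change should be recorded.
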